### Patients

Patient eligibility is assessed at the pre-operative anesthesia consultation. All eligible patients must sign a specifically designed informed consent form.

Male and females, American Society of Anesthesiologists I-II-III, from 18 to 85 years old, scheduled to use patient-controlled analgesia (PCA) with morphine for postoperative pain control after major abdominal surgery by laparotomy (gastric surgery, bilious-pancreatic surgery, hepatic resections, bowel resections, nephrectomy, or any laparotomy with intra-peritoneal access) are enrolled.

Regular use of opioid analgesics, history of drugs or alcohol abuse (or both), postoperative hospitalization in intensive care with sedation or mechanical ventilation (or both), neurological disorders, any heart conduction disease, any cognitive or mental disorder hindering a patient from providing informed consent, body mass index of more than 30, diabetes (type I or II), allergy to study drugs, and use of epidural analgesia are exclusion criteria.

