All patients are evaluated at the end of surgery, at 3, 6, 12, 24, 36, and 48 h, and daily to the seventh postoperative day or until catheter removal by the Acute Pain Service and twice a day by the surgeons as part of their current clinical practice. Pain values, analgesic consumption, any drug-related side effect, and any catheter-related complication (such as occlusion or dislodgment) are recorded. Patients are also evaluated by surgeons after discharge, as in the current practice: any infection or healing retardation is monitored, together with any pain or sensorial abnormality to be signaled to the pain practitioners. Regardless, the Acute Pain Service investigates pain persistence at 1 and 3 months through a phone call, and patients with PPSP (patients experiencing pain at 1 or 3 months after surgery) are eventually referred to our pain clinic for evaluation and treatment.

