### Study outcomes

The primary outcome of the study is to investigate whether a wound infusion of local anesthetic and steroid has a higher analgesic efficacy compared with placebo during 7 days following surgery, assessed as analgesic consumption: the primary endpoint will be the reduction of morphine equivalents required in the first 7 days after surgery.

Secondary outcomes will include the differences in analgesia and side effects within 7 days after surgery. We will investigate any difference in pain at rest and movement (i.e., coughing and deep inspiration) by Numeric Rating Scale (11-point scale from 0 = no pain to 10 = worst imaginable pain), additional analgesic consumption, side effects (postoperative nausea and vomiting, sedation, and any signs of local anesthetic or steroid systemic toxicity), and incidence of persistent post-surgical pain. Differences in terms of wound healing or wound infections will be also assessed up to 3 months to assess any local side effect of steroid infusion. The degree of inflammatory response/oxidative stress between groups will be assessed to analyze the effect of CWI with either treatment or placebo. We plan to analyze the combined effect of some polymorphisms (by using a gene-candidate approach) of genes related to the development of PPSP, pain sensitivity, opioid response, and inflammatory reaction.

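### The only printed definition of persistent post-surgical pain counts any pain at 1 or 3 months, so pain that predates or is unrelated to surgery enters a secondary outcome and a genetic phenotype

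*Protocol article*

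**What the plan says.** The definition stands in the Methods, in the section on the two treatment groups, within the account of evaluations and follow-up: "patients with PPSP (patients experiencing pain at 1 or 3 months after surgery". It sits in a sentence about referral to the pain clinic, but the article prints no other definition. Ascertainment is by telephone: "the Acute Pain Service investigates pain persistence at 1 and 3 months through a phone call".

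The pain evaluations listed in the same section begin after the operation: "All patients are evaluated at the end of surgery, at 3, 6, 12, 24, 36, and 48 h, and daily to the seventh postoperative day". Contact before surgery does exist, but only its screening role (with consent) is described: "Patient eligibility is assessed at the pre-operative anesthesia consultation". Among the exclusions in the Patients section, the one closest to prior pain reads "Regular use of opioid analgesics, history of drugs or alcohol abuse (or both"; chronic or pre-operative pain is not itself listed.

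PPSP is used in two ways. Study outcomes names it as a secondary outcome ("and incidence of persistent post-surgical pain"), and the candidate-gene analysis in that section concerns "genes related to the development of PPSP, pain sensitivity, opioid response, and inflammatory reaction". Reducing PPSP is also among the aims in the last paragraph of the Discussion. The Statistics section gives Pearson's chi-squared test for categorical group comparisons, and Fisher's exact test and logistic regression for the genetic work.

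**The concern.** A patient can enter the trial with abdominal pain from the disease being operated on, or with long-standing pain elsewhere managed without regular opioids. If that pain is still there at a call, the printed rule makes the patient a PPSP case whatever the infusion did.

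Two analyses are affected, in different ways.

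- **Group comparison.** Such cases arise in both arms alike and pull the risk ratio towards 1. A real effect on PPSP would be understated and harder to detect.
- **Genetic comparison.** Genotype is not randomized against pain history. The Background describes some ADRB2 variants as predisposing to chronic pain, and ADRB2 is one of the genes to be typed. A variant that only marks pain present before surgery could then appear to predict pain caused by surgery.

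Timing matters because a pre-operative pain state cannot be reconstructed reliably one to three months later.

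**Working it through.** The article gives no figure for PPSP, so there is nothing of the plan's own to reproduce. What follows is an illustration on assumed rates.

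**Inputs**
- Number per arm: 50, the figure that the Statistics section gives before attrition. It was set for morphine consumption, not for PPSP.
- True PPSP related to surgery, p: 20 % control, 10 % treatment (assumed).
- Pre-existing or unrelated pain still present at a call, q: 5, 10, 20 or 30 %, equal in both arms and independent of true PPSP (assumed).

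**Group comparison**

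Observed rate = 1 − (1 − p)(1 − q). The observed risk difference is therefore the true difference times (1 − q). Power is the unpooled normal approximation, two-sided 5 %:

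power = Φ( d / √[(a(1 − a) + b(1 − b)) / 50] − 1.96 ),

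where a and b are the observed control and treatment rates and d = a − b.

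| q | a | b | d | Risk ratio b/a | Power, 50 per arm |
|---|---|---|---|---|---|
| 0 | 20 % | 10 % | 10 points | 0.50 | 29 % |
| 5 % | 24 % | 14.5 % | 9.5 points | 0.60 | 23 % |
| 10 % | 28 % | 19 % | 9 points | 0.68 | 19 % |
| 20 % | 36 % | 28 % | 8 points | 0.78 | 14 % |
| 30 % | 44 % | 37 % | 7 points | 0.84 | 11 % |

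Worked example, q = 10 %: a = 1 − 0.80 × 0.90 = 0.28 and b = 1 − 0.90 × 0.90 = 0.19. The standard error is √[(0.2016 + 0.1539)/50] = 0.0843. Then 0.09/0.0843 − 1.96 = −0.89, and Φ(−0.89) = 0.19.

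With a pooled variance under the null the powers are 29, 22, 18, 13 and 11 %. The risk ratios do not depend on the number per arm.

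**Genetic comparison: a spurious association**

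Let true PPSP be 20 % in both genotypes, so the true odds ratio is 1.
- Prior pain 20 % in carriers, 10 % in others: observed 1 − 0.80 × 0.80 = 36 % and 1 − 0.80 × 0.90 = 28 %. Odds ratio (0.36/0.64)/(0.28/0.72) = 1.45.
- Prior pain 30 % vs 10 %: observed 44 % and 28 %. Odds ratio (0.44/0.56)/(0.28/0.72) = 2.02.

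**Genetic comparison: dilution**

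If true PPSP is 20 % vs 10 % by genotype, the odds ratio is (0.20/0.80)/(0.10/0.90) = 2.25. With 10 % prior pain in both genotypes it becomes (0.28/0.72)/(0.19/0.81) = 1.66. The error can therefore run in either direction.

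**The case against.** **A condensed article cannot show that a baseline is absent.** The listed evaluations are the Acute Pain Service's rounds, not a full visit schedule, and a pain history may be taken at the consultation. This stands. A reader might infer that the trial makes no pain assessment before surgery; the article supports only that none is described. The definition is different: it is stated, not left out, and as printed it would not use a baseline even if one were recorded.

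**The wording serves referral, and the outcome's name implies a link to the operation.** A broad trigger for referral is reasonable, and no sentence tells staff to count long-standing back pain. This lowers the certainty that such cases would be counted. It does not remove the problem, because nothing else printed tells the caller or the analyst what to count.

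**Randomization protects the group comparison.** Correct. A reader might infer a bias towards one arm; the design does not support that, since prior pain is balanced in expectation. The cost is attenuation and lost power on one secondary outcome.

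**The comparison is weak anyway, and q may be small.** Also fair. At 20 % vs 10 %, power is about 29 % with perfect classification, so the definition is not the main reason for low power. Surgery may remove some disease-related pain, and excluding regular opioid users removes some chronic pain. At q = 5 % the risk ratio still moves from 0.50 to 0.60.

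**A strict wound-site rule would lose visceral pain caused by the operation.** This stands, and the fix below allows for it.

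**Conclusion.** The point holds as a defect in a stated definition. Applied as printed, it counts pre-existing or unrelated pain as PPSP. On the assumed 20 % vs 10 %, with 5 to 30 % unrelated pain, the risk ratio moves from 0.50 to between 0.60 and 0.84, and power falls from an already low 29 % to between 23 % and 11 %. The direction of the attenuation depends only on unrelated pain being equally common in both arms; its size depends entirely on rates that the article does not give.

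The genetic analysis is the more exposed of the two, because a false association can arise there and randomization gives no protection.

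It would go too far to conclude that the main result is at risk: the primary endpoint, morphine equivalents over 7 days, does not use PPSP. The change is worth making, but the trial does not depend on it.

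**What to change.** 1. At the pre-operative anesthesia consultation, record whether pain is present, its site and its Numeric Rating Scale score. This precedes randomization, so it is a valid baseline covariate.
2. At the 1- and 3-month calls, ask the site of any pain and when it began.
3. For analysis, define PPSP as pain in the operated area (wound or abdomen) that is new or worse than before surgery. Naming the abdomen keeps visceral pain arising from the operation.
4. Adjust the genetic analysis of PPSP for pre-operative pain.
5. Keep the any-pain definition as a sensitivity analysis, and leave its use for referral unchanged.
6. For patients already enrolled, take pre-operative pain from the anesthesia record where available.

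The cost is a few questions at contacts that already take place, and a line on the case report form. Trial status reports 46 patients enrolled, against 120 in the Abstract, so 120 − 46 = 74 could still have a baseline recorded prospectively. The downsides are an incomplete baseline for those already enrolled and a lower PPSP incidence, hence fewer events. If the full protocol already records pre-operative pain, only the definition and its use in the analysis need to change.

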### Statistics

Sample size calculation was made on the hypothesis that the average morphine equivalent consumption in patients receiving local anesthetic and steroids CWI will be reduced by 50 % as compared with those in the control group. This assumption comes from (1) our retrospective experience and audits about analgesic consumption in our institution and (2) data from previous literature [27]; they both showed reduction in morphine consumption of 30–50 % in patients receiving local anesthetic wound infusion. Given this assumption, we need 50 patients per group for a power of 80 % and an α error of 5 %; given an attrition rate of 15–20 %, 120 patients are needed in each group.

We will perform an intention-to-treat analysis, and all participants will be analyzed once enrolled. We consider a “dropout” to be any patient not completing the evaluation at 3 months (for any reason).

For descriptive variables, we plan to use mean and standard deviation for normally distributed variables and average interquartile range for skewed distributions.

We will perform group comparison by using the Student’s *t* test or Mann–Whitney test for quantitative variables and Pearson’s chi-squared test for categorical variables. Inflammation, oxidative stress, and genetic background will be assessed to see whether they are biological markers that help modulate post-operative and persistent pain: the difference in inflammatory response and oxidative stress will be analyzed by means in a uni- and multi-variate regression model for repeated measures, including time, group, and their interaction. Variables will be transformed if needed to satisfy model assumptions. Post-hoc comparisons will include within-group changes over time and between-group differences at each assessment. The *P* value will be adjusted for multiple tests. Fisher exact test will be used to evaluate the impact of genetic background. The odds ratio and 95 % confidence interval will be computed with logistic regression. The *P* value to assess statistical significance will be corrected with the Bonferroni correction depending on the number of candidate genes tested.

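### The only definition of persistent post-surgical pain is pain at 1 or 3 months; if used for analysis, pain that has resolved by 3 months counts as persistent

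*Protocol article*

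**What the plan says.** The follow-up paragraph of the Methods (the last one before the genetic study) sets two assessments: "the Acute Pain Service investigates pain persistence at 1 and 3 months through a phone call". The same sentence then says who is to be referred to the pain clinic, namely those with PPSP, whom it describes as "patients experiencing pain at 1 or 3 months after surgery". Nothing else in the article says who has PPSP.

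Study outcomes lists "incidence of persistent post-surgical pain" among the secondary outcomes and attaches no time point. The Abstract (Methods/Design) names PPSP incidence as one of the outcomes to be related to genotype, next to morphine consumption and the inflammatory response. The closing paragraph of the Discussion gives a reduction of PPSP as an aim.

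The Statistics section treats as a dropout "any patient not completing the evaluation at 3 months (for any reason", sizes the trial "given an attrition rate of 15–20" %, and states that "all participants will be analyzed once enrolled". Binary outcomes fall under Pearson's "chi-squared test for categorical variables". No section says how a patient with a 1-month answer but no 3-month answer is classified for PPSP.

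**The concern.** The outcome is meant to capture pain that lasts. A rule that is met by pain at either call cannot separate pain that lasts from pain that fades between the two calls. If treatment, or a genotype, acts mainly on resolution between 1 and 3 months, the combined outcome shows little of it. If it acts mainly on early pain, the combined outcome can show a difference in persistence that is absent at 3 months.

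The same wording has a consequence for incomplete follow-up. One painful call settles a patient's status as a case; status as a non-case needs both calls. A missed 3-month call therefore has a different effect depending on the 1-month answer. At stake are the between-group comparison of PPSP and the PPSP part of the genetic analysis.

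**Working it through.** The article gives no PPSP rate, effect or power, so there is no figure of the plan's own to reproduce. All pain rates below are assumptions. The total of 120 patients comes from the Abstract and the Discussion; 60 per arm assumes equal allocation; tests are taken as two-sided at 5 %. (Statistics speaks of 120 per group. That is a separate inconsistency; 50/(1 − 0.15) = 59 and 50/(1 − 0.20) = 63 per group fit 120 in total.)

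**1. Equal resolved pain in both arms.** Let p be the proportion with pain at 3 months and r the further proportion whose pain is present at 1 month and gone by 3 months. Incidence under the 1-or-3-month rule is p + r. Take p = 20 % versus 10 %, 60 per arm, and the normal approximation for two proportions.

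| r in each arm | Incidence | Risk ratio | Power |
|---|---|---|---|
| 0 (3-month pain only) | 20 % vs 10 % | 0.50 | 33 % |
| 10 % | 30 % vs 20 % | 0.67 | 24 % |
| 20 % | 40 % vs 30 % | 0.75 | 21 % |
| 30 % | 50 % vs 40 % | 0.80 | 19 % |

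The absolute difference stays at 10 points throughout. With p = 30 % versus 15 %, power goes from 50 % to 42 %, 38 % and 37 %. With 40 % versus 20 %, it goes from 67 % to 61 %, 59 % and 61 %. The loss is about 6 to 14 points.

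**2. Unequal resolved pain.** The distortion can run either way.
- Masking: 40 % have pain at 1 month in both arms, half versus a quarter of them still have it at 3 months, and there is no new pain. Pain at 3 months is 0.40 × 0.50 = 20 % versus 0.40 × 0.25 = 10 %; the combined rule gives 40 % versus 40 %.
- The reverse: pain at 3 months is 10 % in both arms and resolved pain is 30 % versus 10 %. The combined rule gives 10 + 30 = 40 % versus 10 + 10 = 20 %, although 3-month pain does not differ.

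**3. Loss after the 1-month call.** Let a = 40 % be in pain at 1 month, q = 5 % of the others develop pain by 3 months, and d be the proportion lost between the calls, unrelated to pain.
- True 1-or-3-month incidence: a + (1 − a)q = 0.40 + 0.60 × 0.05 = 43.0 %.
- Observed, if lost pain-free patients are left unclassified: [a + (1 − a)(1 − d)q] / [a + (1 − a)(1 − d)].
- d = 15 %: 0.4255/0.910 = 46.8 %. d = 20 %: 0.424/0.880 = 48.2 %.
- If lost pain-free patients are counted as non-cases instead, the numerators alone apply: 42.6 % and 42.4 %, a slight understatement.
- Same true incidence in both arms, loss of 20 % versus 10 %: 48.2 % versus 0.427/0.940 = 45.4 %, a spurious 2.8 points.

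**4. Patients touched.** 0.15 × 120 = 18 and 0.20 × 120 = 24. This is a ceiling: it assumes that every dropout answered the 1-month call. With a = 40 %, those left undetermined would be at most 0.60 × 18 ≈ 11 to 0.60 × 24 ≈ 14.

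**The case against.** The definition stands in a sentence about referral, where a broad criterion is understandable. Investigating persistence at 1 and at 3 months is also compatible with reporting incidence at each call. A reader might infer that the protocol fixes the pooled rule as the analysis endpoint. It does not say so, and a fuller plan may set a time point. What remains is that the sentence says in terms who has PPSP, and that the article then uses the term as an outcome without replacing that meaning. So the point concerns a stated definition that suits the outcome badly, and not a detail left out.

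A reader might also infer that the plan prescribes unequal handling of missed calls. It states no classification rule, and its dropout definition does not depend on 1-month status. The asymmetry is only a logical consequence of the word *or*.

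Three further limits stand. The 40 % versus 40 % example is a chosen extreme. The direction is open: if treatment also lowers 1-month pain, the combined outcome may gain power. And PPSP is one of several outcomes of the genetic analysis, not its sole outcome.

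Finally, 3-month pain has a weakness of its own, because patients in pain at 1 month may have been referred and treated by then.

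**Conclusion.** The point holds, conditionally: if the only stated definition is used for analysis, resolved pain is counted as persistent, and a treatment or genotype difference in persistence can be diluted or distorted. Under the assumed rates with equal resolved pain in both arms, the absolute difference is preserved, the risk ratio moves towards 1, and power falls by about 6 to 14 points at 60 per arm. Leaving lost pain-free patients unclassified raises the observed incidence by about 4 to 5 points at 15–20 % loss, on the assumed 40 % and 5 % pain rates.

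The documents do not support a claim that an effect would always be hidden or that incidence would always be inflated. Nor is 18–24 a count of affected patients; it is an upper bound. The primary endpoint, morphine equivalents over 7 days, is untouched. Separating the time points would not make PPSP a well-powered comparison either: 20 % versus 10 % at 3 months has 33 % power.

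**What to change.** Leave the referral wording as it is and add a definition for analysis:

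- For the between-group comparison and the PPSP part of the genetic analysis, PPSP is pain reported at the 3-month call.
- Pain at the 1-month call is reported as a separate outcome.
- Missed 3-month calls are handled by one rule whatever the 1-month answer. A sensitivity analysis uses the 1-month data, so that all enrolled patients are accounted for, in line with the stated intention-to-treat principle.

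This takes a few sentences and no new data, since both calls are already made. Trial status reports 46 patients enrolled, so the definition can still be set before any comparison by group. The cost is fewer events and wider intervals at 3 months. Because 3-month pain may also reflect treatment given after referral at 1 month, the report should say so and show the 1-month result beside it.

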### Procedures - genetic study

We will genotype several SNPs in *ADRB2*, *OPRM1*, *COMT*, *UGT2B7*, and *IL-1Ra* genes in all patients by the Taqman SNP Genotyping Assays (Applied Biosystems, Foster City, CA, USA) in the Pain-OMICS core-lab of Azienda Ospedaliera of Parma.

The peripheral blood samples are collected during general anesthesia into EDTA-coated tubes. We extract DNA by using a QIAamp DNA Blood Mini Kit (Qiagen, Hilden, Germany) from 200 μl of blood. DNA obtained are stored at −20 °C for subsequent TaqMan analysis. Amplification is performed in a volume of 5 μl containing 10 ng of genomic DNA, SsoFast Probes Supermix (Bio-Rad Laboratories S.r.l, Segrate, Italy). Cycling and hybridization conditions are set in accordance with the instructions of the manufacturer.

The amplification and genotyping discrimination are performed in a LightCycler 480 Real-Time PCR System (Roche Diagnostics Ltd, Lewes, UK). All assays are used in accordance with the instructions of the manufacturer (Life Technologies, Monza, Italy). The SNP calling is made with LightCycler 480 Endpoint Genotyping software version 1.5.0.39 (Roche Diagnostics Ltd).

### Procedures - inflammatory response study

Inflammatory response will be analyzed on the first 15 patients in each group (for a total of 30 patients). Before the end of surgery, the surgeon inserts a single-use and minimally invasive (diameter of 0.5 mm) micro-dialysis catheter in the fat adjacent to the surgical wound with sterile technique. The catheter has a cutoff membrane (length of 30 mm) of 100,000 Da, which allows the monitoring of inflammation in vivo. The catheter’s characteristics allow extended use without risk of breaking. The catheter will be connected to a slow-rate infusion pump with imposition of 3 μl/min of micro-dialysis liquid, a high molecular weight (30 g dextran 60/1000 ml) substance to facilitate the micro-dialysis that remains inside the catheter. The dialyzed liquid is collected in dedicated tubes directly in the infusion pump. Sampling will be performed at 1, 6, 24, 48, and 72 h. Serum samples at the same time points are collected to compare systemic and local inflammations. All samples are stored at −80 °C until analysis. Concentrations of ILs (IL-1, IL-6, IL-8, and IL-10), interferon-gamma, and tumor necrosis factor-alpha are analyzed in dialyzed wound samples (local inflammation) and in serum (systemic inflammation). Cytokine levels in dialyzed liquid and in serum are tested by enzyme-linked immunosorbent assay (ELISA) by using a commercial kit.

